### Family navigation

The FN intervention will be co-designed with our SSC, including both theoretical and practical elements. Through co-design, we will maximize child- and family-centeredness, pragmatism, and intervention relevance by co-creating health services *with* and *for* children, caregivers, and clinicians [65].

Our participatory approach draws on key elements of Experience-Based Co-Design (EBCD) [66], an orientation that focuses on understanding SSC members’ experiences with health services, identifying potential improvements, and making changes together. With co-design, we increase intervention relevance and appropriateness, bringing together people who possess experiential knowledge (children, caregivers) with people who have expert knowledge (clinicians, researchers); the two knowledge systems enrich each other. Our team members have substantial experience in co-designing and refining health services and interventions in partnership with stakeholders [67–71].

Our two clinics will have a navigator to deliver FN. Navigators will be trained and equipped with resources for individualized support to benefit families in managing pediatric obesity. Navigators will start by orienting families to the intervention and completing a detailed needs assessment, highlighting areas for support to manage barriers and remove constraints to accessing pediatric obesity management. Strategies used by the navigator may include (i) communicating via text message to schedule appointments, providing appointment reminders, celebrating successes, exploring solutions for barriers to care, and sharing educational resources; (ii) having flexible navigator appointments (evenings, weekends, virtual); and (iii) providing parking/transit passes in-person visits of families with navigators, clinicians, and researchers.

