To evaluate attrition and measures of study rigor and conduct (objective 2), we will compare outcomes against pre-set success indicators. We have a conceptual definition of attrition (permanently discontinue care [19]), but a universal, operational definition does not exist [16, 17]. For this reason, our operational definition will include three categories: “yes,” “no,” and “unknown,” which will be recorded identically for experimental (FN + Usual Care) and control (Usual Care only) groups. If a child discontinues pediatric obesity management at any point up to 12 months post-baseline or if an appointment is missed or cancelled without rescheduling and we have no follow-up communication with the family after four phone/text messages over 4 weeks and no scheduled upcoming appointments, they will be categorized as “yes.” If a child remains active in pediatric obesity management at 12 months post-baseline, they will be classified as “no.” If their status cannot be confirmed, they will be classified as “unknown.” The exact date of attrition will be pinpointed as a child’s last recorded interaction with a pediatric obesity management clinician or navigator, confirmed via primary (child’s medical record, clinic scheduling system) and secondary sources (families, clinicians, navigators [experimental group only]).

In addition, we will measure several secondary outcomes given their established or possible links to attrition [80–85], which will be collected for descriptive purposes and hypothesis generation. RCs will review children’s medical records to retrieve sociodemographic and clinical data, using standard case report forms and processes that adhere to recommendations for medical record reviews to optimize accuracy [86, 87]. For child- and caregiver-reported data, families will complete gender-neutral surveys created using REDCap that will be accessible virtually by desktop, tablet, or smart phone.

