2.What proportion of participants approached were eligible?			≥ 90% approached were eligible		
3.Did recruited participants complete consent/assent procedures?			≥ 95% recruited participants completed consent/assent procedures		
4.Did recruitment lead to successful enrollment?			100% sample size goal achieved		
5.Did participants agree to randomization?			≥ 95% participants agreed to be randomized		
6.Did randomization yield equality across groups?			Equal numbers of participants randomized to experimental and control groups		
7.Were blinding procedures effective?			100% analysts remained blinded to group assignment		
8.Were outcome assessments completed?			≥ 95% participants retained in the study completed outcome assessments		
9.How complete were outcome assessments at all study measurement intervals?			≥ 95% outcome assessments were complete		
10. Were outcome assessments burdensome for families?			≥ 90% children and caregivers disagreed that outcome assessments were burdensome		
11. Was study protocol acceptable to children and caregivers?			≥ 90% children and caregivers agreed study protocol was acceptable		
12. Was the level of attrition adequate within experimental (Family Navigation + Usual Care) and control (Usual Care only) groups at 12 months?			Experimental (FN + UC): 15–25% attrition Control (UC): 30–40% attrition		
13. Was collection of attrition data adequate to calculate sample size for definitive RCT?			≥ 95% participants had attrition data collected by 12 months post-baseline		
14. Were logistics of running a multi-center trial assessed?			Review procedures (ongoing and end-of-grant) with investigators, research staff, navigators		
15. Did all components of the protocol work together adequately?			Review procedures (ongoing and end-of-grant) with investigators, research staff, navigators		

^a^Comments and Feasibility Data columns will be populated with study data collected during our study; example provided for context

^b^Criteria column thresholds based on objective criteria (when possible) and experience gained through study implementation as well as data analysis and interpretation with Stakeholder Committee and research team

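### The attrition date and its confirming sources draw on navigators, who exist only in the FN arm, and the yes/no rule does not exclude navigator contact

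*Protocol article*

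**What the plan says.** The operational definition of attrition is in the Protocol article under Data collection and management. It has three categories (yes, no, unknown), "which will be recorded identically for experimental (FN + Usual Care) and control (Usual Care only) groups".

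There are two routes to 'yes'. The first is that the child discontinues obesity management at any point up to 12 months. The second starts from an appointment missed or cancelled without rescheduling, and requires "no follow-up communication with the family after four phone/text messages" over 4 weeks and nothing further scheduled. 'No' means still active in obesity management at 12 months.

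The date of attrition is the child's "last recorded interaction with a pediatric obesity management clinician or navigator". It is confirmed from the medical record and the scheduling system, and from "secondary sources (families, clinicians, navigators [experimental group only".

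The Family navigation section lists, among the navigator's possible strategies, "communicating via text message to schedule appointments, providing appointment reminders". It also describes navigator appointments, held weekly to monthly, as an addition to clinician appointments. The Background says that navigation deals with barriers and social support and is not itself clinical care.

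**The concern.** The article's concept of attrition is permanently leaving care. Navigator contact is not clinical care by the article's own account, and only one arm can have it. If it enters the outcome, part of any FN versus Usual Care difference would reflect who was in touch with a navigator, not who stayed with the obesity clinicians.

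This matters even in a descriptive feasibility study. Attrition yes/no at 12 months is the named primary outcome, its 95% CI is to be used in the power calculation of the definitive trial (Data analyses), and it is judged against arm-specific bands (Table 2, criterion 12). The research coordinators who collect study data know the assignment (Randomization and blinding), so any room for interpretation is settled by unblinded staff.

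**Working it through.** **1. The date rule.** Let C be the last clinician interaction and N the last navigator interaction.

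- Usual Care: date = C.
- FN: date = max(C, N), which is never earlier than C.

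For the same clinician history, the FN date is equal or later. This follows from the rule and needs no assumption.

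**2. The status rule, term by term.**

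| Term that decides status | Limited to obesity clinicians? | Navigator activity that could count |
|---|---|---|
| Follow-up communication (second route to 'yes') | No | Texts and other replies to the navigator |
| Scheduled upcoming appointments (second route to 'yes') | No | Navigator appointments; Health services lists the navigator as an appointment type |
| Remaining active ('no') | Not expressly | Continuing navigator visits |
| Discontinuing obesity management (first route to 'yes') | Not expressly, but can be so read | None, if navigation is not clinical care |

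Take an FN family that no longer attends clinicians but still answers the navigator. On a broad reading of the first three rows it avoids the second route. On the natural reading of the fourth row it is 'yes'. The text does not say which reading prevails.

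**3. The plan's own figure.** Sample size gives a 95% CI width of at most 0.34 for the difference, with control attrition up to 0.40 and 54 per arm. The FN rate is not given there. Taking 0.20, the midpoint of the 15–25% band in Table 2:

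2 × 1.96 × √[(0.40×0.60 + 0.20×0.80)/54] = 3.92 × 0.0861 = 0.337.

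The stated figure is reproduced and is not in dispute.

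**4. Size per child.** One reclassified FN child moves the FN rate by 1/54 = 1.85 points.

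**5. Illustrations of the contact effect.** The documents give no share of FN dropouts who stay in touch with a navigator, so the shares below are assumptions. With no FN effect and true attrition of 35% in both arms, observed FN attrition is 0.35 × (1 − share):

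| Assumed share masked | Observed FN attrition | Spurious difference |
|---|---|---|
| 10% | 31.5% | 3.5 points |
| 20% | 28.0% | 7.0 points |
| 30% | 24.5% | 10.5 points |

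The upper limit of the FN band (25%) would be reached at a share of 1 − 0.25/0.35 = 28.6%, or 0.286 × 0.35 × 54 = 5.4 children.

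**6. Effect on the next trial, same caveat.** Assume two-sided 5% and 80% power. A true 35% versus 25% needs 329 per arm. If 20% of FN dropouts are masked, FN appears as 0.25 × 0.80 = 20%, and the calculation gives 138 per arm. At 138 per arm the power for the true difference is

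Φ{[0.10 − 1.96√(2×0.30×0.70/138)] / √[(0.2275+0.1875)/138]} = Φ(−0.15), about 44%.

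**7. Information can act the other way.** A navigator may turn an FN 'unknown' into a confirmed 'yes' while a similar control child stays 'unknown'. Criterion 13 asks for attrition data on at least 95%, which allows 5 of 108 without data (103/108 = 95.4%). Suppose all 5 are control children who truly left, and that 'unknown' is omitted (both assumptions). Control attrition then falls from 19/54 = 35.2% to 14/49 = 28.6%, which is 6.6 points against FN.

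**The case against.** The strongest reply is that the navigator wording governs only the date, while the primary outcome is binary and the article describes no time-to-event analysis. The assurance of identical recording is attached to the three categories, not to the date. The first route to 'yes' already covers a child who leaves obesity management, and navigation is not obesity management by the article's own description. A Usual Care family that answers the four messages also avoids the second route.

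Much of this stands. It limits the certain effect to the date and makes the effect on yes/no status an ambiguity. It does not remove the ambiguity: neither discontinuing nor remaining active is tied to clinician encounters, the date rule in the same paragraph treats navigator contact as an interaction that counts, and no other set of sources is named for status.

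Some stronger readings are tempting but unsupported:

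- A reader might infer that FN families text a navigator weekly to monthly. That frequency belongs to appointments; texting is one possible strategy, with no frequency given.
- A reader might add that navigator fields defeat the criterion that "analysts remained blinded to group assignment", or that the yes/no outcome fails to place 'unknown'. Masking of fields and handling of 'unknown' are commonly left to the analysis plan or data-management documents, which are not at hand, so neither is a finding here.

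**Conclusion.** The point holds in limited form. Ascertainment differs by arm in the date rule and in the confirming sources, and this sits badly with the statement of identical recording. The date rule can only leave FN dates unchanged or make them later. For the primary yes/no outcome, the wording permits but does not require a reading that keeps navigator-only families out of 'yes'.

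A reader might infer that the outcome as a whole is shown to be biased towards FN. The documents do not support that: navigator-only contact would favour FN, but navigator information could work in either direction, and the net size cannot be derived. Only the 1.85 points per reclassified FN child is free of assumption; the masked shares and the omission of 'unknown' in the illustrations are assumed.

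Should-fix, moderate confidence, chiefly because this outcome feeds the definitive trial.

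**What to change.** Amend the operational definition as follows:

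- In both arms, derive status and date from encounters with obesity-management clinicians and from scheduled clinician appointments. Include clinician appointments rebooked through a navigator: rebooking is part of how FN is meant to work, and removing every navigator entry could discard genuine returns to the clinic.
- State that navigator-only contacts and navigator-only appointments do not count as an interaction, as follow-up communication, as an upcoming appointment or as being active.
- Use the same confirming sources in both arms for the main analysis.
- Keep navigator contacts as exposure data, and use navigator information on status or date only in a labelled sensitivity analysis.

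The cost is a few sentences of protocol wording and one data-handling rule; appointment type is already tracked (Health services). The downside is slightly less information in the FN arm and possibly a few more 'unknown' classifications, which count against the 95% attrition-data criterion in Table 2.

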#### Clinical

Children’s weight (nearest 0.1 kg) and height (nearest 0.1 cm) will be collected to calculate BMI, BMI percentile, and BMI *z*-score [61]. Families will complete questionnaires on (i) health-related quality of life (HRQoL) assessed by child (self-report; 8–12 years and 13–18 years versions) and caregiver (proxy report) using the PedsQL 4.0 [88] and the Health Utility Index-3 (HUI-3) [89]; (ii) child- and caregiver-reported experienced and implicit weight-related stigma [90]; (iii) Working Alliance Inventory to quantify the strength of therapy relationship between both caregivers and navigators as well as caregivers and clinicians [91]; (iv) caregiver-reported treatment expectations for pediatric obesity management [83]; (v) child and caregiver motivation to change lifestyle and behavioral habits [92]; and (vi) caregiver-rated healthcare satisfaction using the PedsQL Healthcare Satisfaction Generic Module 3.0 [93]. RCs will document harms (i.e., adverse events ([AEs]), which may reveal unintended intervention effects. We will work with our SSC and Trial Steering Committee (TSC) to identify a list of potential harms related to managing pediatric obesity. Broader than adverse events, our list of potential harms will include unintended consequences experienced by families in FN + UC and UC groups.

#### Health services

RCs will track family health care use, including appointment (i) frequency (count); (ii) type (e.g., navigator, physician); (iii) mode (e.g., videoconference, in-person); (iv) duration (e.g., 15-min intervals); and (v) changes (e.g., cancelled, missed). Data will be retrieved from children’s medical records and electronic scheduling systems.

#### Health economics

We will collect descriptive data for future planning, estimating costs for FN intervention development (e.g., mentoring navigators), intervention delivery (e.g., session frequency), healthcare resource use (e.g., physician visits), and family-related time lost (e.g., travel). To inform future economic evaluations, we will use the HUI-3, which measures eight domains of HRQoL and generates a health utility score to calculate quality-adjusted life years (QALYs) associated with each intervention under an area under the curve approach.

#### Sociodemographic data

We will collect birth date, relationship between child and caregiver, ethnicity, and socioeconomic status by self-report from families on the case report form (based on Statistics Canada classifications). Children and caregivers will report their sex at birth [94] and gender [95] according to Statistics Canada definitions.

### Participant incentives

Families will be offered $25 (CAN) gift cards at each data collection time point.

### Data analyses

To inform any modifications before our definitive RCT, we will compare study data to pre-set feasibility criteria (Table 2). For objective 1 (measuring acceptability), we will perform a theoretically informed analysis of interview data using the Theoretical Framework of Acceptability (TFA; [96]). Our theoretically informed analysis situates the professional knowledge of the researcher, allows transparent examination of the research by the reader, and has two main characteristics: how data are structured and how data are interpreted [97]. The structure of our analytic process will be anchored in the theoretical framework. We will interpret the meaning of participants’ words vis-à-vis the theory while allowing new themes to develop. Our analysis will begin after the first interview and be ongoing during the study. RCs at each site will conduct initial coding, using TFA as a guide to structure themes while remaining open to identifying new themes, with line-by-line analysis. Initial findings will be shared with our SSC for review and discussion, then applied to the full data set. In analyzing the full data set, we will remain open to identifying new themes not accounted for in the TFA, reflecting our sensitive use of theory to guide analysis. For rigor and transparency, we will complete the Consolidated Criteria for Reporting Qualitative Research (COREQ) [98].

**Table 2 Tab2:** Acceptability and study rigor and conduct data, with thresholds for assessing feasibility of future definitive randomized controlled trial

Methodological issues	Comments^a^	Feasibility data^a^	Criteria^b^	Feasible? (Y/N)	Need to modify pre-RCT? (Y/N)
1.Was the Family Navigation intervention acceptable to children and caregivers based on the 7 domains from the Theoretical Framework of Acceptability (TFA), including: a. Affective attitude b. Burden c. Perceived effectiveness d. Ethicality e. Intervention coherence f. Opportunity costs g. Self-efficacy	(e.g., data from 1-on-1 interviews)	(e.g., data will be analyzed using thematic analysis, which precludes quantification; 7 themes, plus additional sub-themes)	For each of the 7 domains, findings will be reviewed, discussed, and interpreted with our Stakeholder Committee and research team to determine whether parts of the Family Navigation intervention should remain unchanged or if changes are needed before implementing in our definitive RCT	(e.g., “yes” for all 7 domains)	(e.g., “yes” for 1 domain; “no” for 6 domains)
2.What proportion of participants approached were eligible?			≥ 90% approached were eligible		
3.Did recruited participants complete consent/assent procedures?			≥ 95% recruited participants completed consent/assent procedures		
4.Did recruitment lead to successful enrollment?			100% sample size goal achieved		
5.Did participants agree to randomization?			≥ 95% participants agreed to be randomized		
6.Did randomization yield equality across groups?			Equal numbers of participants randomized to experimental and control groups		
7.Were blinding procedures effective?			100% analysts remained blinded to group assignment		
8.Were outcome assessments completed?			≥ 95% participants retained in the study completed outcome assessments		
9.How complete were outcome assessments at all study measurement intervals?			≥ 95% outcome assessments were complete		
10. Were outcome assessments burdensome for families?			≥ 90% children and caregivers disagreed that outcome assessments were burdensome		
11. Was study protocol acceptable to children and caregivers?			≥ 90% children and caregivers agreed study protocol was acceptable		
12. Was the level of attrition adequate within experimental (Family Navigation + Usual Care) and control (Usual Care only) groups at 12 months?			Experimental (FN + UC): 15–25% attrition Control (UC): 30–40% attrition		
13. Was collection of attrition data adequate to calculate sample size for definitive RCT?			≥ 95% participants had attrition data collected by 12 months post-baseline		
14. Were logistics of running a multi-center trial assessed?			Review procedures (ongoing and end-of-grant) with investigators, research staff, navigators		
15. Did all components of the protocol work together adequately?			Review procedures (ongoing and end-of-grant) with investigators, research staff, navigators		

^a^Comments and Feasibility Data columns will be populated with study data collected during our study; example provided for context

^b^Criteria column thresholds based on objective criteria (when possible) and experience gained through study implementation as well as data analysis and interpretation with Stakeholder Committee and research team

For objective 2 (measuring attrition; study rigor and conduct; clinical, health services, economic outcomes), we will describe continuous data by summaries (means, medians, ranges) and categorical variables with frequency distributions. Data will be described for each group (e.g., sex, gender), stratification (e.g., age [6–9 years, 10–13 years, 14–17 years]), and clinic (Calgary, Mississauga). Group differences in outcomes will be calculated with 95% CIs. To complete power calculations for our definitive RCT, the 95% CI for the primary outcome (attrition yes/no at 12 months post-baseline) will be used. *R* [99] will be used for statistical analysis by a data analyst blinded to group assignments. Our SSC will discuss and contextualize study findings. REDCap will house quantitative data and generate data files for analyses. Consistent with feasibility studies [56], our analyses will be descriptive. Uncertainty exists on what elements(s) of FN are essential to optimize intervention effects [43]. In response, the participatory nature of our research, inclusion of qualitative and quantitative data sources, and heavy participation of our SSC will provide a full assessment of FN, revealing vital insights into how our experimental intervention can optimize treatment impact for managing pediatric obesity in our future definitive RCT.

Qualitative data analysis will occur throughout the study. Quantitative data analysis will occur at study completion only. Based on literature reviews of attrition and pediatric obesity management [16, 17], subgroup analyses will be exploratory and descriptive. We will describe attrition and other outcomes (e.g., HRQoL, intervention dose received) in experimental and control groups to explore potential differences by age, sex, gender, clinic, and changes within and between these subgroups over time.

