**Methods:**

In our 2.5-year study, 108 6–17-year-olds with obesity and their caregivers will be randomized (1:1) to FN + Usual Care or Usual Care after they enroll in obesity management clinics in Calgary and Mississauga, Canada. Our Stakeholder Steering Committee and research team will use Experience-Based Co-Design to design and refine our FN intervention to reduce families’ barriers to care, maximizing the intervention dose families receive. FN will be delivered by a navigator at each site who will use logistical and relational strategies to enhance access to care, supplementing obesity management. Usual Care will be offered similarly at both clinics, adhering to expert guidelines. At enrollment, families will complete a multidisciplinary assessment, then meet regularly with a multidisciplinary team of clinicians for obesity management. Over 12 months, both FN and Usual Care will be delivered virtually and/or in-person, pandemic permitting. Data will be collected at 0, 3, 6, and 12 months post-baseline. We will explore child and caregiver perceptions of FN acceptability as well as evaluate attrition, recruitment, enrolment, randomization, and protocol integrity against pre-set success thresholds. Data on clinical, health services, and health economic outcomes will be collected using established protocols. Qualitative data analysis will apply thematic analysis; quantitative data analysis will be descriptive.

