### Sample size

We will recruit 108 participants (54 per group and per site). Feasibility studies do not include formal sample size calculations [56], but experts recommend 12–36 per arm [59, 60]. We will enroll 27 participants per arm per site. This sample will give a 95% CI of width ≤ 0.34 for the difference in group proportions, assuming attrition is ≤ 0.4 in the control group. A sample size of 54 per arm will also allow 95% CIs of width ≤ 0.29 for other outcomes (e.g., proportion recruited). The sample size calculation for our future definitive RCT will be based on data from this feasibility study.

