### Randomization and blinding

Our team biostatistician will computer-generate a permuted-block randomization sequence using child age on the day of consent (6–9 years, 10–13 years, 14–17 years) and clinic (Edmonton, Calgary, Mississauga) as subgroups to achieve balance across ages and clinics. The randomization sequence will be uploaded to Research Electronic Data Capture (REDCap) for centralized online randomization. Research coordinators (RCs) will then enter participant details into REDCap and manage randomization at each site.

We will conduct our study to reduce the risk of errors, follow best practices for real-world trials [63], and apply pediatric-specific recommendations to minimize the risk of bias [64]. To minimize selection bias, our online allocation process will be managed by team members not delivering interventions. RCs will collect study data to minimize response bias. Data analyses will be led by team members with no family contact. Our team biostatistician will create the randomization sequence but be blind to group assignment to minimize detection bias. RCs, navigators, clinicians, and families will know group assignment. Virtual appointments, which will remain the most common appointment type throughout our study, will limit interactions between families, minimizing ascertainment bias.

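### Table 2, criterion 6 accepts only exactly equal arm totals, which correctly run stratified permuted blocks would usually miss by a few participants

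*Protocol article*

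**What the plan says.** In the Protocol article, Data analyses, Table 2, criterion 6 asks: "Did randomization yield equality across groups". The threshold beside it is "Equal numbers of participants randomized to experimental and control groups". The row then has one yes/no column for feasibility and another for whether a change is needed before the definitive trial. Most of the other numerical rows carry a minimum percentage or a range; this one has no margin.

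The abstract says that families "will be randomized (1:1) to FN + Usual Care or Usual Care". Randomization and blinding describes a "permuted-block randomization sequence using child age on the day of consent" in three bands (6–9, 10–13 and 14–17 years), and by "clinic (Edmonton, Calgary, Mississauga) as subgroups to achieve balance across ages and clinics". Study setting names two recruiting sites, Calgary and Mississauga. Sample size gives 108 participants in total, 54 per group and 54 per site, and adds: "We will enroll 27 participants per arm per site". The article states neither a block size nor a quota per age band.

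Footnote b to Table 2 says that the thresholds rest on objective criteria where possible, and also on experience during the study and on interpretation with the Stakeholder Committee and research team.

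**The concern.** Within a stratum, permuted blocks return to exact balance only when a block is complete. When recruitment closes, any stratum can be partway through a block, and the leftover differences add up across strata. The design controls how large the arm difference can become, whereas the criterion asks for no difference at all.

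The row is meant to tell the team whether the randomisation procedure can go into the definitive trial unchanged. As worded it is a poor test in both directions. A sequence followed without error can miss the threshold by chance, and a 54:54 split does not show that the uploaded sequence was followed.

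**Working it through.** **Plan's own figures.** 27 per arm per site × 2 arms × 2 sites = 108, and 27 × 2 sites = 54 per arm. These reproduce. The article gives no probability of meeting criterion 6, so there is none to check against.

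**Inputs from the article.** 1:1 allocation; three age bands; two recruiting sites, so 3 × 2 = 6 active strata; 54 per site.

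**Assumptions.** Block size (not stated), varied over 2, 4, 6, 8 and mixtures. Stratum totals random (multinomial) within each site, with age shares of one third each.

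**Formula.** A complete block contributes zero. If m children (0 < m < b) have been allocated in the last block of size b, the number G allocated to Family Navigation is hypergeometric, P(G = g) = C(b/2, g) × C(b/2, m − g) / C(b, m), and that stratum contributes D = 2G − m. The arm difference is the sum of D over the six strata. Its distribution was obtained exactly by convolution.

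**Hand check for blocks of 2.** Only strata with an odd count contribute, each ±1. With 54 (even) per site and three strata, the number of odd strata per site is 0 or 2, with probability close to 1/4 and 3/4. Over two sites:

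- 0 odd strata: probability 1/16, P(equal) = 1
- 2 odd strata: probability 6/16, P(equal) = 1/2
- 4 odd strata: probability 9/16, P(equal) = 6/16 = 0.375

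Sum: 0.0625 + 0.1875 + 0.2109 = 0.461.

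**Results, in % of correctly run randomisations.**

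| Block size | Exactly 54:54 | Differ by ≤ 2 | ≤ 4 | ≤ 6 |
|---|---|---|---|---|
| 2 | 46.1 | 93.0 | 100 | 100 |
| 4 | 35.4 | 83.3 | 98.1 | 99.9 |
| 6 | 30.2 | 75.5 | 94.7 | 99.3 |
| 8 | 26.7 | 69.4 | 91.1 | 98.3 |
| mixed 2/4 | 38.3 | 86.5 | 98.9 | 100 |
| mixed 4/6 | 32.0 | 78.4 | 96.1 | 99.6 |

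**Sensitivity.**

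- Age shares of 20/45/35%: unchanged to within 0.2 percentage points.
- Only the total of 108 fixed, not 54 per site: 45.1% (blocks of 2) to 26.7% (blocks of 8).
- All nine listed age-by-clinic strata active: 37.1%, 29.0% and 24.6% for blocks of 2, 4 and 6.
- Odd total enrolment: 0%.
- Every one of the six strata filled to exactly 18: 100% for blocks of 2 or 6, 28.4% for blocks of 4, 24.6% for blocks of 8, and 55.1% for mixed 2/4.

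**Effect of a small imbalance on precision.** With equal outcome variance in the arms, 56:52 gives a variance ratio of (1/56 + 1/52) / (2/54) = 1.0014, so the confidence interval widens by 0.07%. For 57:51 the ratio is (1/57 + 1/51) / (2/54) = 1.0031, or 0.15%. With attrition of 0.40 in control and 0.20 in Family Navigation (the middle of the article's 15–25% band), the Wald 95% width at 54:54 is 2 × 1.96 × √((0.24 + 0.16)/54) = 0.337. With 51 in control and 57 in Family Navigation it is 2 × 1.96 × √(0.24/51 + 0.16/57) = 0.340; with the arm sizes reversed it is 0.336.

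**The case against.** The strongest reply is that nothing practical follows from the wording. Footnote b allows interpretation with the committee and team, the need to modify is a separate column from feasibility, the analyses are descriptive, and the article has no rule by which one missed row stops the definitive trial. A 55:53 split would probably be discussed and passed over. This stands as a limit on the consequence. A reader might infer that a miss would automatically declare the randomisation infeasible and in need of change; the article does not say that. The footnote gives no margin for this row, however, and deciding what is close enough after seeing the split defeats the purpose of a pre-set threshold.

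A second reply is that block size and stratum quotas are details an article may leave to the full protocol. The planned interviews with 36 children aged 10–17 out of 54 in the Family Navigation group fit equal thirds by age, and strata filled to exactly 18 with blocks of 2 or 6 would always balance. That is possible, but the article describes only an expected age mix and writes no quota. The percentages are therefore conditional on assumptions and are not fixed properties of the design.

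Two further inferences should be avoided. The 27 per arm per site is a sample-size target; criterion 6 concerns only the two arm totals, so equality within sites is not its test. Nor do most strata necessarily end on an incomplete block: with blocks of 2, on average only about half do.

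**Conclusion.** The point holds as a minor one. Given random stratum totals and an even final total, a correctly run randomisation meets the written threshold less than half the time for every block scheme tried. With six strata and 54 per site, the range for a single block size is 46% (blocks of 2) down to 27% (blocks of 8). With blocks of 2 the miss rate is only about 54%, so the statement that it would usually miss is narrow there and firmer for larger blocks. It would not hold if strata were filled to 18 with blocks of 2 or 6.

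The fault lies in the threshold. A reader might conclude that the randomisation method itself is unsound or that the attrition estimate is at risk, and neither follows: differences of 2 to 6 participants arising by chance from a concealed sequence introduce no bias and hardly change the interval width.

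**What to change.** Replace the threshold in criterion 6 with: every allocation matches the uploaded sequence, and arm totals differ by no more than a margin set in advance from the actual block sizes and number of strata. A margin of 6 is one example; with six strata, correct randomisation meets it over 99% of the time for blocks up to 6 and about 98% of the time for blocks of 8. The sequence check tests the REDCap set-up directly, which equal totals cannot do.

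The cost is one table row and no new data. It does alter a pre-set criterion after recruitment began in October 2022, so the Trial Steering Committee, which approves amendments, should agree the margin before the quantitative analysis at study completion and without sight of the arm totals. Whoever sets the margin should also confirm how many clinic strata the sequence uses, since the randomisation section lists three clinics and the study has two sites.
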